# Can on-line gait training improve clinical practice? Study protocol for feasibility randomised controlled trial of an on-line educational intervention to improve clinician’s gait-related decision-making in ambulant children and young people with cerebral palsy

**DOI:** 10.1186/s40814-024-01477-5

**Published:** 2024-05-14

**Keywords:** Instrumented gait analysis, Gait analysis, Cerebral palsy, Physiotherapy, Paediatric physiotherapy, Educational intervention, Clinical education, Randomised controlled trial, Protocol

## Abstract

**Background:**

Instrumented gait analysis (IGA) is an assessment and research tool with proven impacts on clinical decision-making for the management of ambulant children and young people with cerebral palsy (CYPwCP) but is underused and variably understood by relevant clinicians. Clinicians’ difficulties in gaining expertise and confidence in using IGA are multifactorial and related to access for clinical decision-making, limited training opportunities and inability to translate this training into clinical practice.

**Methods:**

The primary aim of this study is to test the feasibility of an educational intervention to advance clinicians’ application of gait analysis in CYPwCP, to inform a definitive trial. The secondary aim is to measure the effect that appropriate IGA training has on physiotherapists’ knowledge, skills, confidence and behaviours. This will be a two-arm feasibility randomised controlled trial with an experimental and control group. The 6-week on-line intervention uses a multicomponent approach grounded in behavioural change techniques. A repeated measures design will be adopted, whereby participants will complete outcome measures at baseline, immediately after the intervention and at 4 months. The primary outcome measures (trial feasibility-related outcomes) are recruitment and engagement. The secondary outcome measures (trial research-related outcomes) are knowledge, skills, confidence and practice change. Outcome measures will be collected via online questionnaires and during observed skill assessments. Analysis of data will use descriptive statistics, two-way mixed ANOVA model and qualitative content analysis.

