### Trial design

This will be a two-arm feasibility randomised controlled trial with an experimental and control group. The 6-week on-line intervention delivered as part of the trial is a stand-alone, post-graduate level educational course called Virtual Gait Analysis Course for Paediatric Physiotherapists (VGAPP). Eligible physiotherapists who consent to take part in the study will be randomly allocated into experimental and control groups. A repeated measures design will be adopted, whereby participants will complete outcome measures at baseline, immediately after the intervention, and at 4 months. This will include collection of feedback as part of a full process evaluation.

The trial will be determined feasible if a priori set criteria based on primary outcome measures and included in the process evaluation will be achieved at or above agreed levels (see the ‘Outcome measures’ section of ‘Methods’). After conducting and reviewing outcomes of the full evaluation process, the decision about delivery of the definitive trial will be made.

Figure 1 shows the study flow diagram, and Table 1 indicates the schedule of enrolment, intervention, and outcome measures [18].

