***Primary***			
Recruitment	Study will recruit 24 participants	Number of participants	Descriptive statistics
Retention	Study will retain 75% of sample	Number of participants	Descriptive statistics
Engagement	The average proportion of completed VLE items will be ≥ 66%	Average proportion of completed VLE items	Descriptive statistics

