***Secondary***			
Knowledge	EG will have improved knowledge scores relative to CG EG will increase knowledge scores EG will maintain knowledge scores	MCQ test	Effect sizes and 95% CIs from repeated measures ANOVA test and Kruskal–Wallis *H*-test
Skills	EG will have improved practical skills scores relative to CG EG will increase practical skills scores EG will maintain practical skills scores	OSCE	Effect sizes and 95% CIs from repeated measures ANOVA test and Kruskal–Wallis *H*-test
Attitudes	EG will have improved gait-related practice behaviours	Questionnaires: Self-reported knowledge and confidence, practice change, practice change planning, beliefs, semi-structured interviews	Effect sizes and 95% CIs from repeated measures ANOVA test Framework method for qualitative data (Ritchie 2014)
Satisfaction	EG will demonstrate a high satisfaction rate	Satisfaction questionnaire	Descriptive statistics

*EG* experimental group, *CG* control group, *VLE* virtual learning environment, *MCQ* multiple-choice question, *OSCE* observed standardised clinical examination

Recruitment will be determined as feasible if study is able to recruit 24 participants within 4 months [22, 23]. Retention rates will be considered at two stages: (1) from expression of interest to consent — it will be deemed feasible if greater than 50%, and (2) from consent to course completion — it will be deemed feasible if greater than 75% [24, 25]. Additionally, engagement (participants’ interactions with an online system) data will be collected during intervention via the analytics tools in the QMUL Virtual Learning Environment which log the detail of activity access, time, and completion for each component. These analytic tools are part of the general-purpose dashboard and provide an algorithmic representation of student online behaviours based on whether the behaviour occurred and for how long, rather than quality of these behaviours. Previous studies show that these analytics have been positively correlated with student performance [26–28]. It will be deemed feasible if the average proportion of completed learning sessions and tasks will be ≥ 66%.

Secondary outcomes are as follows: knowledge, skills, attitudes, and satisfaction will be collected via online questionnaires (SurveyMonkey) and during skill tests (OSCE). Knowledge, skills, and attitudes will be collected at three timepoints (Table 1).

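### The feasibility rule treats exactly 75% retention as a pass in one place and a fail in another, and leaves the standing of the interest-to-consent criterion unclear

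*Protocol article*

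**What the plan says.** **Trial design** gives the rule: "The trial will be determined feasible if a priori set criteria based on primary outcome measures and included in the process evaluation will be achieved". Each criterion has to reach or exceed its agreed level. It sends the reader to the Outcome measures section for those levels, and adds that the decision on the definitive trial follows a review of the full evaluation.

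**Outcome measures** states the levels twice.
- Table 3, primary rows: "Study will recruit 24 participants", "Study will retain 75% of sample", and mean completion of online items of at least 66%.
- Text below the table: "Recruitment will be determined as feasible if study is able to recruit 24 participants within 4 months". Retention is then judged in two stages. The first, "1) from expression of interest to consent", must be more than 50%. The second, from consent to finishing the course, must be more than 75%. Engagement is again at least 66%.

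**Abstract, Methods:** "The primary outcome measures (trial feasibility-related outcomes) are recruitment and engagement". Retention is not named and no levels are given.

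**Process evaluation and implementation outcomes** counts recruitment, retention and engagement thresholds as feasibility measures and refers back to Methods.

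**The concern.** Whether a definitive trial is feasible is the primary aim, so the pass levels are the main decision rule of the study. On retention, the rule in Trial design and the text of Outcome measures give opposite answers at the boundary, and with 24 participants that boundary is an attainable count. The interest-to-consent level appears in the text but not among the primary targets in Table 3, so a reader cannot tell whether missing it alone would make the trial not feasible. The Discussion names poor uptake and drop-out as main challenges, and these are the quantities concerned. If the wording is left open until the data are in, the choice of inequality could be made with the result in view.

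**Working it through.** **Planned size.** Sample size gives at least 12 per arm: 12 × 2 = 24. This matches the recruitment target and the number to be enrolled under Participant timeline.

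**The statements side by side.** Trial design's rule for every criterion is to reach or exceed the agreed level.

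| Criterion | Table 3 | Text below Table 3 |
|---|---|---|
| Recruitment | 24, no period given | 24 within 4 months |
| Interest to consent | not listed | more than 50% |
| Retention after consent | 75% | more than 75% |
| Engagement | at least 66% | at least 66% |

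**Retention boundary at N = 24.** Table 3 carries no inequality sign. Read with Trial design, it means at least 75%.
- At least 75%: 0.75 × 24 = 18, so 18 retained is enough.
- More than 75%: 18/24 = 75.0% fails and 19/24 = 79.2% passes, so 19 are needed.

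**How likely the conflict is.** Let X be the number retained, taken as binomial with n = 24 and true retention p. The values of p are assumptions, since the protocol gives none. All 24 are taken as the denominator and participants as independent. The rules disagree only when X = 18, with P(X = 18) = C(24,18) p^18 (1 − p)^6.

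| Assumed p | P(X ≥ 18) | P(X ≥ 19) | P(X = 18) |
|---|---|---|---|
| 0.70 | 0.389 | 0.229 | 0.160 |
| 0.75 | 0.607 | 0.422 | 0.185 |
| 0.80 | 0.811 | 0.656 | 0.155 |
| 0.85 | 0.943 | 0.861 | 0.082 |

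**Other sample sizes.** Exactly 75% is attainable only if N is divisible by 4. Otherwise both wordings need the same count: 19 of 25, 20 of 26, 21 of 27, 23 of 30.

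**Interest to consent.** With 24 consents, more than 50% allows at most 47 expressions of interest (24/47 = 51.1%). At 48 the proportion is exactly 50% (24/48), which fails the text's wording but would pass a reach-or-exceed rule. From 49 upwards (24/49 = 49.0%) it fails either way. Table 3 has no such criterion, so it is silent in all these cases.

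**The case against.** A reader might infer that the Abstract, Table 3 and the text are three competing sets of go/no-go criteria, from which the one that passes could be picked afterwards. The documents do not support that.
- The Abstract names outcome domains without any level, and Trial design points to Outcome measures, not to the Abstract. A verdict by the Abstract alone can be reached only by borrowing levels from elsewhere.
- Table 3 is captioned as a summary. Its missing recruitment period reads most naturally as a shortening of the 4-month criterion beneath it.
- Engagement agrees in both places.
- The final decision follows a wider evaluation, so one participant need not settle it.
- The retention split arises only at some totals, and 24 is described as a minimum.

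All of this stands, and it narrows the point. It does not remove the retention conflict. The cross-reference leads to a section whose text uses a strict inequality, while the sentence making the cross-reference uses a non-strict one, and shortening cannot explain that. Nor does calling Table 3 a summary tell the reader whether the criterion it leaves out is decisive. The wider evaluation does not make the pass level itself any clearer.

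**Conclusion.** The point holds in a limited form. The feasibility rule is inconsistent on retention: at the planned 24, exactly 18 retained is feasible under Trial design with Table 3 and not feasible under the text. The chance of that result is about 0.08 to 0.19 for assumed true retention of 70% to 85%. At an assumed 75%, the chance of passing is 0.607 under one wording and 0.422 under the other. These figures rest on a final total of 24, all of them in the denominator, and independent participants. The go/no-go standing of the interest-to-consent criterion is undetermined whatever the sample size. The recruitment period missing from Table 3 and the retention outcome missing from the Abstract are inconsistencies to tidy, not separate decision rules.

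**What to change.** Before analysis, write one list of go/no-go criteria and use it in Trial design, Table 3 and the text of Outcome measures:
- recruitment of 24 within 4 months;
- retention with a single inequality, for example at least 75%, which would match the rule in Trial design;
- interest to consent (50%) either listed as a criterion, with its inequality, or labelled descriptive;
- engagement of at least 66%, unchanged.

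Add retention to the primary outcomes named in the Abstract. The cost is wording only: no change to design, data collection or sample size.

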**Discussion:**

This study will determine feasibility of the definitive randomised control trial of educational intervention delivered to advance clinicians’ application of gait analysis in CYPwCP. This study offers the shift in emphasis from regarding IGA as a tool to a focus on clinicians’ requirements for access, training and a well-defined role to optimise utilisation of IGA. The impact of this should be better engagement with IGA and clinical practice change. This study will contribute to a body of educational research into clinical education of healthcare professionals and IGA training offering insight into high levels of evaluation evidence including clinical behaviour change.

**Trial registration:**

Protocol has been registered with the Open Science Framework (osf.io/nweq6) in June 2023.

**Supplementary Information:**

The online version contains supplementary material available at 10.1186/s40814-024-01477-5.

## Background

The National Institute for Clinical Excellence (NICE) refers to instrumented gait analysis (IGA) assessment as a preferable choice prior to gait-improving orthopaedic surgery [1]. The impact of IGA on decision-making in treatment planning and treatment outcomes for ambulant CYPwCP has been broadly debated in the literature particularly in areas of orthopaedic decision-making [2–5] and individually tailored nonsurgical treatments [6, 7]. Generally, single event multilevel surgeries (SEMLS) are performed after IGA is conducted as the IGA results can help to determine which specific soft-tissue or bony surgical procedures should be performed [8]. Furthermore, studies show that use of IGA for treatment decision-making has potential to improve patient outcomes — authors indicate the positive gait-related outcomes and improvement in gait parameters when treatment matches IGA recommendations [9–11]. Despite this, more standardised access pathways for CYPwCP to IGA are yet to be established [7, 12], and access to the IGA for other professionals involved in gait management such as physiotherapists or orthotists and their formal IGA education remains limited [13]. As a science, gait analysis brings a wide spectrum of knowledge and skills, making it hard to educate and successfully integrate it into undergraduate curricula [14]. Clinicians’ difficulties in gaining expertise and confidence in using IGA are multifactorial and can be related to lack of IGA access for clinical decision-making, limited training opportunities and inability to translate this training into clinical practice [15].

According to research, clinician-centred factors such as IGA training and affiliation to IGA laboratory [16] are shown to influence engagement with IGA-derived recommendations and may therefore impact on patient outcomes [17].

This indicates a required shift in emphasis from regarding IGA as a tool providing 3rd party recommendations to a focus on clinicians’ requirements for access, training and a well-defined role to optimise utilisation of IGA [17]. This is essential to address in order to improve inequity of access and patient outcomes. Findings of our previous research [15, 17] provided context for the design and delivery of a feasibility randomised controlled trial (RCT) of an educational intervention to improve clinicians’ engagement with the IGA.

### Study aims and objectives

The primary aim of this study is to determine the feasibility of an educational intervention to advance clinicians’ application of instrumented gait analysis in children and young people with cerebral palsy, to inform the design of a full trial. Objectives are as follows:

To establish the feasibility of a future randomised controlled trial of educational intervention.Assess the rate of participant enrolment, retention and compliance with intervention.Assess whether the inclusion and exclusion criteria for participants are appropriate.Assess whether the duration of intervention is appropriate.Assess whether intervention delivery in a virtual learning environment is feasible and acceptable.Explore if the outcome measures are appropriate for the study aims.Define the sample size for a definitive trial.Explore the fidelity of intervention delivery.Further understand the barriers and facilitators of the intervention.

The secondary aim is to measure the effect that appropriate IGA training and its delivery has on physiotherapists’ knowledge, skills and attitudes.

## Methods

This feasibility trial protocol follows the SPIRIT statement on defining standard protocol items for clinical trials and its checklist [18] and the CONSORT statement extension to randomised pilot and feasibility trials and its checklist [19].

### Trial design

This will be a two-arm feasibility randomised controlled trial with an experimental and control group. The 6-week on-line intervention delivered as part of the trial is a stand-alone, post-graduate level educational course called Virtual Gait Analysis Course for Paediatric Physiotherapists (VGAPP). Eligible physiotherapists who consent to take part in the study will be randomly allocated into experimental and control groups. A repeated measures design will be adopted, whereby participants will complete outcome measures at baseline, immediately after the intervention, and at 4 months. This will include collection of feedback as part of a full process evaluation.

The trial will be determined feasible if a priori set criteria based on primary outcome measures and included in the process evaluation will be achieved at or above agreed levels (see the ‘Outcome measures’ section of ‘Methods’). After conducting and reviewing outcomes of the full evaluation process, the decision about delivery of the definitive trial will be made.

Figure 1 shows the study flow diagram, and Table 1 indicates the schedule of enrolment, intervention, and outcome measures [18].

**Fig. 1 Fig1:**
[figure not shown]
Study flow diagram

**Table 1 Tab1:** Standard Protocol Items: Recommendations for Interventional Trials (SPIRIT) diagram illustrating the study design and timescales

Design	Study period								
	**Enrolment**	**Allocation**	**Baseline**	**Pre-intervention**	**Intervention (experimental)**	**End of intervention**	**Follow-up 4 months**	**Intervention (control)**	**End of study**
**Enrolment**									
Participant recruitment	x								
Eligibility screen	x								
Informed consent	x								
Allocation		X							
**Intervention**									
Pre-intervention resources				x					
6-week intervention					x				
Live sessions					x				
**Assessments**									
Feasibility outcomes (recruitment)	x		x						
Feasibility outcomes (retention)									x
Feasibility outcomes (VLE data)						x			
Acceptability			x			x	x		
Process evaluation	x		x		x	x	x		x
Demographics			x						
Attitudes			x			x	x		
Satisfaction						x			
Self-rated knowledge			x			x	x		
Self-rated confidence			x			x	x		
Knowledge test			x			x	x		
Practice change						x	x		
Intention to change practice						x	x		
Economic									x

*VLE* virtual learning environment

### Participants

#### Study setting

This study will be conducted virtually using Queen Mary University of London (QMUL) virtual learning environment (VLE), online questionnaires (SurveyMonkey), and Microsoft Teams, eradicating the need for participants to travel, reducing both cost and participants’ time. Participating clinicians will be working in a variety of settings (acute and community, special schools, both national health service and private settings) within the UK, where the data will be collected. Each participant’s data will be collected under their unique student number. To ensure anonymity, once data collection is complete, student numbers will be additionally coded.

#### Eligibility criteria

The aim of the inclusion and exclusion criteria is to ensure that participants are actively involved in assessment and treatment of ambulant CYPwCP and have currently available opportunities to apply the taught knowledge and skills in their workplace. The eligibility criteria were reviewed during the stakeholder focus groups including both clinicians and educators. Focus groups found inclusion and exclusion criteria appropriate for the feasibility trial (see Supplementary material).

Inclusion criteria are as follows:18 years of age or olderPhysiotherapists currently providing assessment and treatment to ambulant children and young people with cerebral palsyPracticing within the UK (any National Health Service or private practice setting)

Exclusion criteria are as follows:Outside of UKNot currently employed as physiotherapist or on a career breakIn rotational posts, where they could rotate to specialty not managing ambulant CYPwCP

### Intervention

#### Design and refinement

This educational intervention uses a multicomponent approach grounded in behavioural change techniques (BCTs). The overall aim of the intervention is to improve gait-related clinical practice.

Intervention (VGAPP) will be delivered via QMUL VLE and will comprise of pre-course resources and a 6-week course. Content of the VGAPP course has been developed based on evidence from the scientific literature, current best practice and informed by the scoping review [17], qualitative study [15] and results from a national survey of paediatric physiotherapists in the UK (unpublished, in review). Stakeholder engagement has been integral to the research and intervention design, delivery and evaluation process and included Patient and Families (PPI-A) interviews and Clinicians and Educators Focus Groups (PPI-B) (Fig. 2). PPI-A included children, young people and their families who have a lived experience of cerebral palsy and received IGA as part of management of their condition. PPI-A was involved in the design of intervention prior to involving clinicians in order to ensure that the project is centred around the needs of patients and to ensure that the practice behaviour change, and transfer of knowledge will directly benefit patients and their families. Themes, subthemes and illustrative quotes from patients and parents’ interviews and changes applied to the intervention and evaluation content are available in the Supplementary Table 1. PPI-B were representatives from all UK nations, with a variety of paediatric physiotherapy specialisms, experience levels and from different work settings, thus providing invaluable insight and the opportunity for further refinement of the intervention design (in the areas of recruitment, eligibility criteria, sample size, control group intervention), content, delivery and evaluation methods. Themes, subthemes, and illustrative quotes from clinicians and educators focus groups and changes applied to intervention and evaluation content are available in the Supplementary Table 2.

**Fig. 2 Fig2:**

Stakeholder engagement

Through this process, several changes were implemented to the intervention content and assessment process in areas of communication, patient/family perspectives, orthotics, and linking elements of gait-related practice to the ICF domains. A detailed PPI involvement report, including the educational intervention refinement process is available from the corresponding author on reasonable request.

